To answer these questions, we will systematically enhance or inhibit activity in frontal or parietal brain regions in healthy older adults during attentional control and prospective memory tasks. We will modulate activity in three areas; that is, the right superior parietal lobe, the right inferior frontal lobe or the left inferior frontal lobe. In order to replicate previous studies, we will test whether attentional control will predict laboratory prospective memory. In addition, we will test whether attentional control will also predict naturalistic prospective memory.

We hypothesize that the right inferior frontal gyrus and the right superior parietal lobe will be important for laboratory prospective memory as well as for attentional control. Modulation of the left inferior frontal cortex, however, will only lead to an improvement in prospective memory since attentional control seems particularly associated with the right hemisphere. Finally, we hypothesize that attentional control will predict laboratory prospective memory rather than self-reports or naturalistic prospective memory. Laboratory tasks share a similar setting and rely on timely motor responses while self-reports or naturalistic prospective memory tasks do not. To control for any effect of mood or agitation on cognition, we will examine current mood as well as the heart rate of all participants.

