### Statistical analysis

Our primary outcome measures will be performance in attentional control and laboratory prospective memory tasks: From the ANT, we will evaluate the controlling variable. From the TAP, we will use the number of false alarms in the Go/No-Go tasks, correct answers in the flexibility task, the number of missed targets in the dual task, and mean reaction times. For laboratory prospective memory, accuracy and reaction times will be evaluated. We will use mixed ANOVAs or mixed effects models for statistical analysis of stimulation effects on primary outcome variables (depending on whether there will be any missing data). In contrast to an ANOVA, mixed effects models are better capable of handling missing data and they also allow an analysis of data on a trial level while taking hierarchical structures of data and variability within subjects into account. We will use session (first, second) as within-subject factor and condition (six experimental groups or sham) as between-subject factor. We will determine whether inhibiting or enhancing activity in the left or right frontal inferior lobe or the right superior parietal lobe will modulate attentional control or prospective memory.

As secondary outcomes, we will evaluate accuracy of the ongoing task as well as ICV of reaction times during attentional control or the ongoing-task of the laboratory prospective memory paradigm. In addition, we will test whether stimulation will have any effect on alerting or orienting (i.e., ANT Task). We will then test whether attentional control significantly predicts laboratory, naturalistic, or self-reported prospective memory using multiple linear regression.

Further we plan to model laboratory prospective memory responses by using multinomial modelling of response probabilities [51]. This approach estimates both the prospective component (i.e., remembering *that* you have to do something) and the retrospective component (e.g., remembering *when* and *what* you have to do) of prospective memory.

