## Discussion

In the current study, we will systematically enhance or inhibit activity in brain regions known to be associated with attentional control and prospective memory. This may contribute to our understanding whether more or less activity in these regions is associated with better attentional control or prospective memory in older healthy adults. We expect that enhancing activity in these brain regions will lead to more accurate and faster responses in laboratory prospective memory and attentional control tasks, due to increased excitability of underlying neurons. In contrast, we expect opposite effects when inhibiting activity. There is some evidence to suggest, though, that increasing the excitability of neurons does not necessarily lead to an increase in cognitive performance. Complex interactions between stimulation type, duration, stimulation strength as well as task characteristics or mood of the participants may play a role [57]. It could therefore be that inhibiting activity in a given region may actually increase task performance, due to an improved signal-to-noise ratio [58]. The theory behind that is that when a stimulus in the environment elicits activity in a brain region, stimulus-irrelevant noise is also present. The higher the signal in comparison to the noise, the more accurate the response of the participant. If stimulation does not enhance the signal-noise ratio but rather reduces it, performance may drop.

Besides performance improvement or worsening, it could also be that we will find differential effects on outcome measures. An increase in accuracy, for example, could be linked to slower responses, or reduced accuracy could be linked to faster responses. Since we will use different attentional control tasks and both laboratory and naturalistic prospective memory tasks, we will be able to disentangle these interactions and discuss possible implications.

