The results of our study will allow future perspectives for non-invasive brain stimulation research in the fields of prospective memory and attentional control in older adults. If attentional control or prospective memory can be enhanced with high-definition tDCS, its feasibility for long-term interventions may be evaluated in the future. A combination of cognitive training and repeated stimulation may, for instance, be promising. A recent meta-analysis by Jones and colleagues [59] found that a cognitive training with memory and/ or attention exercises can be useful for improving prospective memory. These effects may even be enhanced by non-invasive brain stimulation. As tDCS merely modulates brain activity that is already present (e.g., evoked by a task), the stimulation protocol may need to be personalized (e.g., using neuro-navigation) [60]. Compared to conventional tDCS, high-definition tDCS allows focal stimulation and also prevents bidirectional modulation within a brain area [61]. Therefore, predictions of stimulation effects on cognitive outcomes may be more precise and personalized stimulation may be more accurate. The transfer of training or stimulation effects from the laboratory to participants’ daily lives will be a big challenge for future interventions, though.

The results of our study, in particular the predictive value of attentional control for prospective memory, may contribute to this topic. Based on the integrative framework by Zuber and colleagues [2], we expect to find differences in the predictive value, depending on the ecological validity of the prospective memory task. The analysis of the predictive value may also contribute to a better understanding of the ‘age-prospective memory paradox’ which postulates that an impaired prospective memory in older adults is typically found in laboratory, but not in naturalistic tasks [62]. If we find evidence that attentional control is differentially predictive of naturalistic vs. laboratory tasks, this may contribute to the explanation of the paradox and may provide hints on how laboratory prospective memory tasks should be adapted to address similar functions as in naturalistic tasks.

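### The 'rather than' hypothesis about attention and memory is given only separate tests against zero, which cannot show a difference; the left-frontal 'only' hypothesis has the same gap

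*Protocol article*

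**What the plan says.** Two hypotheses in the Introduction are comparative. The first concerns prediction: "we hypothesize that attentional control will predict laboratory prospective memory rather than self-reports or naturalistic prospective memory". The second concerns stimulation: "Modulation of the left inferior frontal cortex, however, will only lead to an improvement in prospective memory"; the reason given is that attentional control is tied mainly to the right hemisphere.

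The Discussion repeats the first as an aim: "we expect to find differences in the predictive value, depending on the ecological validity of the prospective memory task". It then attaches a consequence, beginning "If we find evidence that attentional control is differentially predictive of naturalistic vs. laboratory tasks": such evidence would bear on why older adults do worse in laboratory but not naturalistic tasks.

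The Statistical analysis section gives these analyses:

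- Prediction: "We will then test whether attentional control significantly predicts laboratory, naturalistic, or self-reported prospective memory using multiple linear regression".
- Stimulation: "We will use session (first, second) as within-subject factor and condition (six experimental groups or sham) as between-subject factor", applied to the primary outcomes.
- All models: age as covariate, p < 0.05, Bonferroni-Holm correction.

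The article states no comparison of slopes between memory measures, no term in which outcome domain interacts with condition, and no equivalence margin.

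On left-frontal stimulation the Discussion is broader than the Introduction. It expects that "enhancing activity in these brain regions will lead to more accurate and faster responses in laboratory prospective memory and attentional control tasks", without setting the left-frontal site apart.

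**The concern.** *Rather than* and *only* are statements about a difference between two effects. Every test the article states is of one effect against zero. If the laboratory slope reaches p < 0.05 and the naturalistic slope does not, the natural reading is that the hypothesis is confirmed. Yet the two estimates may be almost the same and fall on either side of the threshold.

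Two conclusions are at stake. One is that attention matters differently for laboratory and naturalistic memory, which the Discussion would carry over to the paradox and to the design of future tasks. The other is that left-frontal stimulation acts on memory but not on attention. Either could be declared where no difference exists.

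**Working it through.** **Inputs.** From the documents: N = 105, 15 per group, p < 0.05 (taken as two-sided). Assumed, because the documents give no values: the true attention-memory correlation r, the same for both memory measures (0.1 to 0.4); the correlation between the memory measures (0.1 to 0.5); one attention predictor, no age covariate, no Holm adjustment. The plan has no figure of its own to reproduce here, since its sample-size calculation concerns the seven-group ANOVA.

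**Step 1. An illustration with made-up estimates.** Take observed correlations of 0.22 (laboratory) and 0.16 (naturalistic), with the memory measures correlated 0.3. Each test is t = r √[(N − 2)/(1 − r²)].

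- Laboratory: 0.22 × √(103/0.9516) = 2.29, p about 0.02.
- Naturalistic: 0.16 × √(103/0.9744) = 1.64, p about 0.10.

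Williams' test of the difference, with N − 3 = 102 degrees of freedom, is

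t = (r₁ − r₂) √{ (N − 1)(1 + r₁₂) / [ 2((N − 1)/(N − 3))|R| + r̄²(1 − r₁₂)³ ] }.

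Here |R| = 1 − 0.0484 − 0.0256 − 0.09 + 2(0.22)(0.16)(0.3) = 0.857 and r̄ = 0.19. So t = 0.06 × √(135.2/1.760) = 0.53, p about 0.6. The separate tests look like a dissociation, but the data say nothing about a difference.

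**Step 2. Closed form, independent results.** By Fisher's z, power p ≈ Φ(atanh(r) √102 − 1.96). The chance of 'laboratory significant, naturalistic not' is p(1 − p).

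- r = 0.20: atanh(r) √102 = 2.05, p = 0.535, so 0.535 × 0.465 = 0.249.
- r = 0.25: atanh(r) √102 = 2.58, p = 0.732, so 0.732 × 0.268 = 0.196.

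This is an upper end. Both measures come from the same people, so the two results are not independent.

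**Step 3. Simulation with correlated memory measures, N = 105, no true difference.**

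| True r (both measures) | Laboratory significant, naturalistic not | Williams' test rejects |
|---|---|---|
| 0.10 | 10–14% | about 5% |
| 0.20 | 17–24% | about 5% |
| 0.25 | 14–19% | about 5% |
| 0.30 | 8–10% | about 5% |
| 0.40 | about 1% | about 5% |

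The ranges span memory-measure correlations of 0.5 (lower rate) to 0.1 (higher rate). If naturalistic and self-reported memory must both be non-significant, as the Introduction's wording implies, the rate is 8–11% at r = 0.20 and about 5% at r = 0.25.

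**Step 4. When a difference exists.** With true correlations of 0.3 and 0.1, and memory measures correlated 0.3, the pattern appears in 72% of trials. The direct test has about 42% power.

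**Step 5. The 'only' hypothesis, 15 v 15, post-test only.** The noncentrality is d √(15 × 15/30) = d √7.5 with 28 degrees of freedom. At d = 0.5 it is 1.37 and power is 0.262, so a real attention effect of that size is missed about 74% of the time. If memory and attention share the same true effect and are treated as independent, 'memory significant, attention not' has probability p(1 − p):

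| d | Power p | p(1 − p) |
|---|---|---|
| 0.2 | 0.083 | 0.076 |
| 0.5 | 0.262 | 0.19 |
| 0.8 | 0.562 | 0.25 |
| 1.0 | 0.753 | 0.19 |

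**The case against.** The strongest reply is that the article never says the hypotheses will be decided by one significant and one non-significant result. A reader might infer such a rule, but it is not written. The Discussion's language about differential prediction is compatible with a direct comparison, and an analysis plan that is not shown could contain one. This stands, and it limits the point to a mismatch between the hypotheses and the tests the article does state. It does not remove the point: the article chooses an analysis for the *rather than* hypothesis, and that analysis alone cannot establish it.

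Four further limits also stand.

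- **Size.** A reader might take 20–25% as the error rate, or 40–50% by counting either measure being the significant one. The first is the independent-results figure near 50% power, where p(1 − p) peaks. The second includes the reverse pattern, which would not support the hypothesis. Holm adjustment and the age covariate would change the figures, but neither turns a test against zero into a test of a difference.
- **Session.** The regression sentence names no session and lists no regressors. A reader might infer that stimulated session-2 scores will be used without adjustment. The documents do not say so, and an article may leave this detail out. It matters only as a refinement of the fix.
- **Left-frontal wording.** The Discussion sentence is a general expectation about the regions as a group, and it is qualified directly afterwards. It is looser than the Introduction and should be aligned, but it is not a formal counter-hypothesis.
- **Power for 'only'.** The 26% ignores the baseline session, which can raise power if the two sessions correlate well.

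**Conclusion.** The point holds for the *rather than* hypothesis. The article's stated regression tests each association against zero, while the conclusion wanted is about a difference between associations. With equal true correlations at N = 105, the supportive-looking pattern occurs in about 1% to 24% of trials, depending on the assumed r. It exceeds the roughly 5% of a direct test for r from 0.1 to 0.3 and falls below it at 0.4. These figures rest on the assumptions listed in the working, not on anything in the documents.

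The *only* hypothesis has the same gap, because outcome domain is not a factor in the stimulation models. With about 26% power at d = 0.5, a non-significant attention result is no evidence of no effect.

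The documents do not support the stronger reading that the sponsor has committed itself to a faulty decision rule. The tests of stimulation effects on each primary outcome are untouched. The correction should be made, but it concerns the comparative claims only.

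**What to change.** 1. **Prediction.** In the Statistical analysis section, state that the comparative claim rests on a direct test of the difference in standardised attention slopes between memory measures, reported with its interval. Suitable methods are a multivariate or stacked regression with an attention-by-measure interaction and within-person correlation, or the Williams or Steiger test for dependent correlations. Orient all measures the same way first.
2. **Data used.** Fit this on session-1 data, before any stimulation, or include condition as a covariate. The self-report questionnaire differs between sessions, so name the one that is used.
3. **Left-frontal 'only'.** Use an outcome-by-condition-by-session contrast on standardised outcomes, comparing the left-frontal groups with sham. Otherwise, do not claim *only* from a non-significant attention result. A left-minus-right contrast on attention alone would not serve, because it never uses the memory outcome.
4. **Wording.** Align the Discussion's expectation for left-frontal stimulation with the Introduction.

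The cost is a few lines of code and text, with no change to design or data collection. The real price is power: about 42% for correlations of 0.3 against 0.1, so the comparative claims may end as inconclusive. The report should say so if that happens.

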### Randomization

A total of 105 healthy older adults will be included, stratified by age and sex. All participants will be randomly assigned to one of six experimental groups or the control condition (i.e., sham stimulation). They will receive anodal or cathodal high-definition tDCS of the right inferior frontal lobe, the left inferior frontal lobe, or the right superior parietal lobe, or sham. For sham stimulation, we will randomly place the electrodes over the same regions. Randomization will be done by JP based on a Matlab script written by TR (allocation ratio 1:5, stratified by age and sex). Neither JP nor TR will be involved in data collection. The study will follow a double-blind design, such that neither the participants nor the experimenter will be aware of the stimulation condition. Unblinding will occur at the end of data acquisition. Exceptions will only be allowed in case of adverse events.

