### Laboratory prospective memory task

We will use an adapted version of an event-based prospective memory task [36] and will again present stimuli with PsychoPy3 (v2021.1.3). The paradigm will consist of an ongoing task as well as a prospective memory task (Fig 4). During the ongoing task, the participants will indicate by button presses whether a word pair belongs to the same semantic category or not. For the prospective memory task, they will additionally need to remember the colour and the letter of a string of letters that will appear instead of a word pair from time to time (i.e., ‘v’ or ‘c’). Whenever one of the subsequent word pairs will be presented in the same colour as the letter string, participants will need to press the respective letter key (e.g., ‘c’; Fig 4). That means, they would need to inhibit a response to the ongoing task (i.e., indicating whether the two words belong to the same category or not). The letter string represents a prospective memory intention that has to be retrieved when a specific event occurs (i.e., event-based prospective memory). At the end of the task, an ongoing-only block will be added. This block will include prospective memory cues that the participants will need to ignore. With the ongoing-only block, we will assess possible aftereffects of prospective memory (i.e., difficulties to inhibit prospective memory intentions). The task will consist of 178 word pairs and 12 letter strings. The ongoing-only block will consist of 38 word pairs, and three (irrelevant) prospective memory letter strings. For the generation of word pairs, we will use a list of 633 words, from which 216 words (belonging to 36 different categories) [37, 38] will be chosen randomly (i.e., half of these will be used for each session). There will be two lists of words (A or B). Each list will contain the same words, either paired with another word from the same category or not. Half of the participants will see list A in the first session and list B in the second and vice versa. The letter strings (i.e., ‘v’ or ‘c’) will be presented for 4 s, either in magenta or in green. The word pairs for ongoing trials will be shown for 3 s in red, blue, white, yellow, cyan, or orange. Between a letter string and a word pair with the corresponding font colour (i.e., magenta or green), 6 to 10 word pairs will be presented. All ongoing-task colour fonts, except orange and cyan, may appear several times between the presentation of two letter strings. Cyan and orange will be used with similar frequency as magenta and green (i.e., prospective memory cue). This will control for effects of low frequency of colours: Words displayed in cyan or orange should be identified as ongoing-task stimuli although they appear equally often as the prospective memory cue colours. Again, task instructions will be provided orally and in writing. The participants will train the task with different word pairs until two prospective memory intentions will be correctly identified. Again, the training will be done immediately before the actual task begins.

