### Naturalistic prospective memory tasks

To assess naturalistic prospective memory, we will adapt the *Royal Prince Alfred Prospective Memory Task* [43]. The task consists of two prospective intentions that need to be remembered during the on-site session as well as two intentions that need to be remembered later at home. We will use two different versions of the task, one for each session (see Table 1). The order of the versions will be counterbalanced across participants. The participants will receive a score in each of these tasks depending on how timely and accurately the intention was retrieved (ranging from 0 = late and incorrect retrieval to 3 = correct and timely retrieval). Participants will be told not to use any external memory aids. The naturalistic tasks will be as follows: The participants will need to alert the experimenter after finishing a specific questionnaire and when five minutes have elapsed. In addition, they will need to leave a message on the study phone as soon as they arrive at home as well as five days after the session. The participants will have to repeat the instructions to guarantee correct understanding. The sum of all scores achieved in the naturalistic prospective memory tasks will be used for statistical analysis.

**Table 1 pone.0289532.t001:** Naturalistic prospective memory tasks used in our study.

	Version A	Version B

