We will include age as a covariate in all models since it significantly influenced prospective memory in our previous study [52]. We will control for any potential influence of mood or agitation on cognition and test, in an exploratory analysis, whether mood or heart rate of participants will influence attentional control or prospective memory. Further we examine, whether one of these two measures are modulated by non-invasive brain stimulation. For an assessment of heart rate, we will include changes in beats per minute (relative to baseline) between the start of stimulation until two minutes after its end (i.e., 22 minutes). Generalized estimated equations will then be used to test any longitudinal stimulation effects on heart rate during the stimulation session [53–55].

We will use R (version 4.2.1) with RStudio (version 2022.02.3) for statistical analyses with *p* < 0.05 considered statistically significant. We will correct for multiple-comparisons using Bonferroni-Holm correction. Whenever the assumptions of normality and homogeneity are not met, data will be transformed and/or non-parametric alternatives will be used. We will only analyse data of participants that attended both sessions.

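### Sex (a stratification factor) and word list (a counterbalanced factor) are not named in the stimulation models, which costs some precision but causes no bias

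*Protocol article*

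**What the plan says.** All of this comes from the protocol article.

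- **Randomization:** "A total of 105 healthy older adults will be included, stratified by age and sex". The allocation note repeats the two factors: "allocation ratio 1:5, stratified by age and sex".
- **Laboratory prospective memory task:** "Half of the participants will see list A in the first session and list B in the second and vice versa". The section adds that the two lists hold the same words, paired within or across categories. The prospective-memory cue is a font colour.
- **Naturalistic prospective memory tasks:** "The order of the versions will be counterbalanced across participants". This score is not among the primary stimulation outcomes.
- **Statistical analysis, model:** "We will use mixed ANOVAs or mixed effects models for statistical analysis of stimulation effects on primary outcome variables", and "We will use session (first, second) as within-subject factor and condition (six experimental groups or sham) as between-subject factor".
- **Statistical analysis, covariates:** "We will include age as a covariate in all models". The same paragraph says that mood and agitation will be controlled for.

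The reason given for age is an earlier result, not its role in the stratification. Sex, word list and list order appear nowhere as model terms.

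**The concern.** When a design balances arms on a factor, the analysis normally carries that factor too. Otherwise its variance stays in the residual although the design has removed it, wholly or partly, from the arm differences. The standard error is then larger than the design requires. Here the article fixes one covariate for every model, which covers one of the two stratification factors and passes over the other.

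The word list matters for a more direct reason. Stimulation is given only in the second session, so its effect is read from the session-by-condition interaction, that is, from differences between arms in session-to-session change. A participant who sees A then B carries the list difference in the change with one sign, and a participant who sees B then A carries it with the other. It does not cancel within a person. It touches accuracy and reaction time in the laboratory prospective-memory task, both primary outcomes. With 15 participants per arm and Holm correction, the trial has little precision to give away.

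**Working it through.** **Inputs from the article.** Seven groups of 15 (105 in all), two sessions, significance level 0.05, age in the model, and only participants with both sessions analysed. The article gives no figure for a sex effect or a list difference, so those sizes below are assumptions. It states no power for this test, so there is no figure of its own to reproduce on this point.

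**Step 1: the test.** With two sessions and one summary value per session, the session-by-condition test is a seven-group F test on change (session 2 minus session 1). With age in the model, it has 6 and 105 − 7 − 1 = 97 degrees of freedom.

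**Step 2: sex.** If sex shifts the outcome by the same amount in both sessions, it drops out of the change. A check on simulated data gave the same interaction p-value with and without such an effect (0.879 both times). Sex matters to this test only if it alters the change itself.

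**Step 3: list.** Let d be the A/B difference in SDs of change. One order group has +d in its change and the other −d, so the two groups differ by b = 2d. With equal halves the added variance is b²/4 = d²:

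- d = 0.125: 0.125² = 0.016, a rise of 1.6%
- d = 0.25: 0.25² = 0.0625, a rise of about 6%
- d = 0.5: 0.5² = 0.25, a rise of 25%

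**Step 4: effect on the test.** Simulation used 20,000 null and 10,000 alternative data sets per setting. The alternative has one group shifted by 1.2 SD of change. Each cell gives the result with the factor omitted, then included.

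| d | b | Balance of order | Type I error | Power |
|---|---|---|---|---|
| 0.125 | 0.25 | within arms | 4.6% / 5.0% | 88.6% / 89.2% |
| 0.25 | 0.5 | within arms | 3.6% / 4.8% | 87.0% / 89.5% |
| 0.5 | 1.0 | within arms | 1.7% / 5.1% | 78.9% / 89.9% |
| 0.125 | 0.25 | overall only | 4.9% / 5.1% | 88.7% / 88.7% |
| 0.25 | 0.5 | overall only | 4.6% / 4.7% | 87.3% / 89.5% |
| 0.5 | 1.0 | overall only | 5.0% / 4.9% | 80.4% / 89.2% |

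The same b applies to sex if it shifts the change by b SDs and the sexes are equally frequent.

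**Step 5: closed-form check.** The noncentrality is 15 × 1.2² × 6/7 = 18.5, and the 5% critical value of F(6, 97) is 2.19. With exact balance within arms, omission multiplies the needed F by 1 + d²:

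- d = 0.125: 2.19 × 1.016 = 2.23, type I error 4.7%, power 89.3%
- d = 0.25: 2.19 × 1.0625 = 2.33, type I error 3.8%, power 87.6%
- d = 0.5: 2.19 × 1.25 = 2.74, type I error 1.7%, power 79.5%

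With the factor included, power is 89.9%. This agrees with the simulation to within about one point.

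**Step 6: uneven splits.** Fifteen cannot be halved, but an 8/7 split moves an arm mean by only d/15, which is 0.5/15 = 0.03 SD at d = 0.5. If order is balanced only overall, the chance list imbalance between two arms has SD d × √(2/15) = 0.37d, or 0.09 to 0.18 SD of change for d from 0.25 to 0.5. This is random error, already reflected in the type I error near 5%, and not bias.

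**The case against.** Several points on the other side are sound.

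- The models do not ignore the design. Age, one of the two stratification factors, is in every model, and mood or agitation is to be controlled for. This stands, and the point is limited to sex and list.
- A reader might infer that leaving out sex makes a nominal 5% test run at 4.4% to 3.4%, from 2·P(Z > 1.96/√(1 − R²)) with R² of 0.05 to 0.15. That is a two-group calculation, and it holds here only if sex explains that share of the variance in **change**. Nothing in the article suggests this, and a sex difference equal in both sessions cancels.
- A list difference of 0.25 to 0.5 SD is not supported by the article. Both lists contain the same words, and the cue is a font colour, while the word pairs belong to the ongoing task. A smaller effect is more plausible on prospective-memory accuracy and reaction time. Equal difficulty is nevertheless not assured, because the pairings differ between lists.
- The list does not bear on the attention network task or the attentional test battery.
- A reader might also infer biased estimates or too many false positives. The calculations show neither: the test is conservative or holds its level.
- The article condenses a fuller plan, which may name these terms, and fixing age in all models does not exclude others. That limits the weight of the point. It does not remove it, because the article sets out the model factors and a covariate for all models, and that statement passes over one of its own stratification factors.

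**Conclusion.** The point holds as a modest matter of efficiency. Sex and word list are balanced by design but not named in the models, so whatever they contribute to session-to-session change stays in the error term.

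The loss is negligible at a list difference of 0.125 SD of change (at most 0.6 power points), 2 to 3 points at 0.25 SD, and 9 to 11 points at 0.5 SD. The upper end is an assumption for which the article offers no support. If the factor is balanced within arms the test is conservative, and if it is balanced only overall the type I error stays near 5%. The article says that half of the participants see each order, without saying half of each arm, so either case is possible.

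These figures assume one value per participant and session, normal errors, complete data and one arm shifted by 1.2 SD. For sex, the cost is zero unless sex affects change.

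**What to change.** State in the Statistical analysis section, before unblinding:

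1. In the stimulation models, enter sex beside age, with a sex-by-session term. Equivalently, enter sex in a change-score or baseline-adjusted model. A sex main effect alone would leave the session-by-condition test as it is.
2. In the laboratory prospective-memory models only, enter the list seen (A or B) as a within-subject factor. In a change-score model, the equivalent is list order.

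The cost is a line or two of text and one or two degrees of freedom per model. Step 5 shows how little that is: with no effect of the added factor, one extra degree of freedom leaves power at 89.9%. Sex and assigned list are already known for every participant, so no new data are needed. Fixing the terms now also prevents a choice of covariates after the results are seen.
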